#### Treatment

Regardless of treatment group, all patients will be scheduled for the first treatment session within 3 days of the baseline examination. All patients will attend 2 therapy sessions in the first week, then 1 session per week for the next 3 weeks for a total of 5 treatment sessions. In each treatment group, the first 2 sessions will begin with delivery of the randomly assigned manual therapy technique followed by a range of motion exercise. The final 3 sessions will involve instruction in a standardized exercise program. The only difference among the 3 groups will therefore be the type of manual therapy technique used in the first 2 sessions. Otherwise the 3 groups will receive the identical treatment.

#### Manual therapy technique for sessions 1 & 2

##### Standard manipulation group

This treatment group will receive the manipulation technique that was used in the development of the CPR [18,20]. The manipulation technique is performed with the patient supine. The therapist stands on the side opposite of that to be manipulated. The patient is passively moved into side-bending towards the side to be manipulated. The patient interlocks the fingers behind his or her head. The therapist passively rotates the patient, and then delivers a quick thrust to the ASIS in a posterior and inferior direction (Figure 2).

We will use the same manipulation decision-making used in validation of the CPR.^34 ^The side to be manipulated will be the more symptomatic side based on the patient's self-report. If the patient cannot specify a more symptomatic side, the therapist may select either side for manipulation. After the manipulation is performed, the therapist will note whether or not a cavitation (ie "a pop") was either heard or felt by the therapist or patient. If a cavitation is experienced, the therapist will proceed to instruct the patient in the ROM exercises. If no cavitation is produced, the patient will be repositioned and the manipulation will be attempted again. If no cavitation is experienced, the therapist will attempt to manipulate the opposite side. A maximum of two attempts per side will be permitted. If no cavitation is produced the therapist will proceed to instruct the patient in the ROM exercises.

##### Alternate side-lying manipulation group

This treatment group will receive an alternative manipulation technique performed with the patient side-lying. The patient will lie with the more painful side up. The therapist stands in front of the patient. The therapist will then flex the top leg until there is movement at the selected segment (eg. L4–L5) interspace and place the patient's foot in the popliteal fossa of the bottom leg. Next the therapist grasps the patient's bottom shoulder and arm and introduces left trunk sidebending and right rotation until motion is felt at the L4–L5 interspace. The therapist's right thumb is then placed on the right side of the L4 spinous process and the patient's arms are positioned around the therapist's right arm. Setup is maintained while the patient is rolled toward the therapist. Finally the therapist's left arm is used to apply a high velocity, low amplitude thrust of the pelvis in an anterior direction (Figure 3).

We will use the same manipulation decision-making for this group. The side to be manipulated first will be the more symptomatic side based on the patient's self-report. If the patient cannot specify a more symptomatic side, the therapist may select either side for manipulation. The therapist will select the spinal level towards which to direct the manipulation based on segmental mobility assessment performed in side-lying or prone. The therapist will chose a segment in the lower lumbar region towards which to direct the manipulation because the lower lumbar spine is more frequently the source of symptoms in patients with LBP, and recent research suggests greater benefits from manual therapy techniques directed towards the lower lumbar spine [22]. In addition, although this manipulation technique is theoretically directed towards a specific lumbar level, recent evidence suggests that the effects are likely not level-specific [28].

Identical to the standard manipulation group, the therapist will note whether or not a cavitation (ie "a pop") was either heard or felt by the therapist or patient after the manipulation is performed. If a cavitation is experienced, the therapist will proceed to instruct the patient in the ROM exercises. If no cavitation is produced, the patient will be repositioned and the manipulation will be attempted again. If no cavitation is experienced, the therapist will attempt to manipulate the opposite side. A maximum of two attempts per side will be permitted. If no cavitation is produced the therapist will proceed to instruct the patient in the ROM exercises. Following the manipulation treatment, all patients will be instructed in the ROM exercises.

##### Mobilization technique group

This treatment group will receive lumbar postero-anterior mobilizations directed at two spinal segments selected by the treating therapist lumbar segments (eg. L4 and L5). Patients receiving this technique will lie prone. The treating therapist will place the hypothenar eminence of one hand over the spinous process of L4. With the elbows remaining extended, the therapist will deliver oscillatory mobilization (grade IV) for 60 seconds (approximately 30 oscillations) [22,29]. Following a 30 second rest the therapist will again repeat the mobilizations (grade IV) directed at L5 for 60 seconds (approximately 30 oscillations) [22,29]. Following another 30 second rest break rest break the therapist will repeat the procedures at L4 and L5 again.

No cavitation is expected to occur in the mobilization group, however if a cavitation is experienced it will be noted by the therapist. Following completion of the mobilization treatment, the therapist will proceed to instruct the patient in the ROM exercises.

#### Procedures common to all groups

##### Range of motion exercise (visits 1–2)

After receiving the manual therapy intervention, patients in all treatment groups will be instructed in a pelvic tilt range of motion (ROM) exercise. The pelvic tilt exercise will be completed in the physical therapy clinic immediately after the manipulation. Subjects are asked to lie on their back and bend the hips and knees so that their feet are flat on the surface. Subjects then attempt to flatten their back on the table by slightly "drawing in" their stomach and rotating the hips backwards without holding their breath. The motion is to be performed in a pain-free range. Subjects will be instructed to perform a set of 10 repetitions in the clinic during the first and second sessions after manipulation and will be instructed to perform 10 repetitions of the exercise 3–4 times daily until the beginning of the third treatment session. Subjects' will self-report their compliance with range of motion exercise program in an exercise log. At the beginning session #3, the therapist will instruct subjects in this group in the standardized exercise regimen.

##### Standardized exercise program (visits 3–5)

Beginning on the third treatment session, all patients will be treated with the same strengthening and stabilization exercise program. The program is based on current evidence from the biomechanical literature [30-33]. The AHCPR Clinical Practice Guidelines for Adults with LBP [34] recommends muscle strengthening exercises for patients with acute LBP, and evidence also supports exercise therapy for individuals with chronic LBP [35]. The exercise program will target the trunk musculature that has been identified as important stabilizers of the spine including transversus abdominus, oblique abdominals, and the multifidus/erector spinae [30-33]. Patients will also be asked to complete the strengthening program once per day on the days they do not complete the exercise program during the physical therapy session. Patients will self-report their compliance with the exercise program in an exercise log.

### Data analysis

We will recruit 60 patients per clinical site, for a total enrollment of 240 patients across the four geographical locations. A sample size of 240 patients will provide 93% power to detect a minimal difference of 5 points on the OSW assuming a common standard deviation of 10 points. A sample size of 60 within each geographical location will provide 83% power to detect a difference of 9 points on the OSW assuming a standard deviation of 10 points. This sample size will provide sufficient power to detect a minimum clinically important difference in the entire sample, and a moderate difference within a geographical location.

Descriptive statistics, including frequency counts for categorical variables and measures of central tendency and dispersion for continuous variables will be calculated to summarize the data. Baseline demographic data will be compared across treatment groups to assess the adequacy of the randomization. If appropriate, statistical adjustments will be made for baseline characteristics that are significantly different between groups. An intention-to-treat analysis will be utilized in which all participants will be analyzed in the group to which they were originally assigned. All drop-outs and the reason for dropping out of the study will be reported. An *a priori *alpha level of 0.05 will be used for all analyses. All data will be screened to ensure they meet the assumptions for the inferential statistical analyses described below. If they do not meet the necessary assumptions, appropriate non-parametric procedures will be utilized.

The primary aim will be tested with analysis of variance (ANOVA) using the change in OSW score from baseline to 4-weeks (OSW_Baseline _– OSW_4-weeks_) as the dependent variable. The independent variable will be treatment with three levels (lumbo-pelvic manipulation, alternative lumbar manipulation, lumbar mobilization). A second ANOVA will be conducted on the one-week OSW change scores to test for the presence of an immediate treatment effect. We will also repeat the ANOVA procedure for the 6-month follow up outcomes, and using pain rating as the dependent variable.

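### The 93% power stated for a 5-point OSW difference is modestly too high for the planned three-group ANOVA: with equal arms it is at most 91%, and 81% if the third arm lies midway

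*Protocol article*

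**What the plan says.** The sample-size statement is in the protocol article, Methods, Data analysis. Recruitment is 60 patients per site, "for a total enrollment of 240 patients across the four geographical locations". The whole-sample claim is that "A sample size of 240 patients will provide 93% power to detect a minimal difference of 5 points on the OSW". The SD behind it is given as 10 points, the same in every group. The companion claim is that "A sample size of 60 within each geographical location will provide 83% power to detect a difference of 9 points on the OSW", with the same SD. The section concludes that these numbers suffice for a minimum clinically important difference overall and for a moderate difference within a site.

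On the test, the same section says: "The primary aim will be tested with analysis of variance (ANOVA) using the change in OSW score from baseline to 4-weeks". Treatment is the only factor and has three levels. On the error rate, an a priori "alpha level of 0.05 will be used for all analyses".

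The article does not state the allocation ratio, the pattern of the three means behind the 5 or 9 points, or the formula used.

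**The concern.** In a two-arm trial, a difference of 5 points fixes the effect completely. In a three-arm trial it does not. The power of the overall F test also depends on where the third arm lies, and the article does not say. The reader therefore cannot tell what the 93% describes. On recalculation, no position of the third arm gives 93% under the planned test with equal arms.

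The figure matters because a null result is plausible. The abstract's Background notes that different manual therapy techniques may give similar outcomes, and the trial is built to examine that. If the ANOVA is not significant, the stated power tells the reader how likely the trial was to miss a 5-point difference. The article implies 100 − 93 = 7%. Under the planned test with complete data it is about 9% (100 − 91.2) to 19% (100 − 81.0).

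**Working it through.** **Inputs.** From Data analysis: N = 240 in total and 60 per site; differences of 5 and 9 points; SD 10; alpha 0.05; one-way ANOVA with three groups. Assumed: equal allocation, so 240/3 = 80 per arm overall and 60/3 = 20 per arm within a site. Complete data are used throughout.

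**Formula.** Power = P(F′ > F critical), where F′ is noncentral F with 2 and 3(n − 1) degrees of freedom and λ = n × Σ(mean − grand mean)² / SD². For means (0, x, d), the sum of squares is (2/3)(d² − dx + x²). It is smallest at x = d/2 and largest at x = 0 or x = d. These two cases therefore bound the power for every pattern whose largest difference is d.

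**Trying to reproduce the 93% (n = 80, d = 5, df 2 and 237).**

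| Means | Sum of squares | λ | Power |
|---|---|---|---|
| 0, 0, 5 (two arms equal) | 16.67 | 80 × 16.67/100 = 13.33 | 91.2% |
| 0, 2.5, 5 (third arm midway) | 12.5 | 80 × 12.5/100 = 10.0 | 81.0% |

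The best case is 93 − 91.2 = 1.8 points short and the midway case is 93 − 81.0 = 12 points short. Treating the variance as known (a chi-square approximation) raises the best case only to 91.5%. Reading the 5 points as the gap between each pair of neighbouring arms (0, 5, 10) gives over 99.9%, so that reading does not produce 93% either.

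**Pairwise comparison.** For a two-sided t-test of 80 against 80, the noncentrality is 5 / (10 × √(2/80)) = 3.16 and power is 88.2%.

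**Per-site figure (n = 20, d = 9, df 2 and 57).**

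| Means | Sum of squares | λ | Power |
|---|---|---|---|
| 0, 0, 9 | 54 | 20 × 54/100 = 10.8 | 82.5% (82.507%, which rounds to 83%) |
| 0, 4.5, 9 | 40.5 | 20 × 40.5/100 = 8.1 | 69.9% |

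The stated 83% is reproduced, but only under the favourable pattern. The same pattern applied to the whole sample gives 91%.

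**Size of the gap in other terms.** A full 93% for 5 points would need 86 per arm (258 patients) under the favourable pattern, or 114 per arm (342) with the third arm midway. With 80 per arm, the largest difference detectable with 93% power is 5 × √(86/80) = 5.2 points in the favourable pattern and 5 × √(114/80) = 6.0 points in the midway pattern.

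**Sensitivity to the allocation assumption.** The 91.2% ceiling holds for equal arms. If the arm that differs held half the patients (120, 60, 60), λ would be 240 × (2.5/10)² = 15 and power 94.1%. Nothing in the article suggests such a split. The same split within a site gives λ = 60 × (4.5/10)² = 12.15 and power 86.9%, which does not match the stated 83%.

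**The case against.** The strongest defence is that the article never commits to a pattern of means. Under the pattern with one arm apart from two equal arms, the planned ANOVA comes within 1.8 points of the stated 93% and reproduces the 83% to rounding. Of the t-test and ANOVA versions tried, that pattern is the only one that comes within 2 points of both figures. On this view the 81% is a sensitivity result under an assumption that the authors did not make, and what remains is loose rounding. Much of this stands. The per-site 83% is not an error, and the 81% alone does not prove one. But 91.2% is the ceiling for equal arms, so 93% is too high even on the kindest reading, and the pattern on which it leans is not stated.

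Three stronger readings are tempting, and the article does not support them:

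- **That the 93% came from a one-sided two-group t-test.** That test does give 93.4%, but it gives 87.5% for the site figure, not 83%. The article names no formula, so the origin of the figure is unknown.
- **That drop-out makes the real power much lower.** The article says only that "All drop-outs and the reason for dropping out of the study will be reported". It gives no expected rate, and an attrition allowance may sit in a fuller document. Any loss would lower power, but a figure for it would be the reader's assumption.
- **That 81% is a guaranteed floor.** It holds only with equal arms, complete data and an SD of 10.

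**Conclusion.** The concern holds in a limited form. With 80 per arm, SD 10, alpha 0.05 and complete data, the planned ANOVA has 81.0% to 91.2% power for a largest difference of 5 points. The stated 93% is therefore overstated by about 2 points at best and 12 at worst. The per-site 83% is correct under the favourable pattern and falls to 69.9% with the third arm midway.

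A reader might infer that the trial is underpowered or that its design is undermined. That does not follow: even the least favourable pattern leaves the whole-sample analysis above 80% with complete data, and the test, alpha and sample size are unaffected. This is a moderate to minor reporting error. It should be corrected because it bears on how a null result is read. The conclusion rests on equal allocation, which the article does not state.

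**What to change.** Reword the sample-size paragraph in Data analysis along these lines:

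> With 240 patients allocated equally (80 per arm), an SD of 10 points and alpha 0.05, the one-way ANOVA has 81% to 91% power with complete data for a largest difference of 5 OSW points between arms, depending on where the third arm lies (91% if two arms are equal, 81% if the third is midway). Within a site (20 per arm), power for a largest difference of 9 points is 70% to 83% on the same basis.

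If allocation is not equal, state the ratio and recompute both figures. If the authors had one pattern of means in mind, name it as the planning assumption and give the matching figure: 91% overall and 83% per site for one arm differing from two equal arms.

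The cost is one paragraph of rewording and a less favourable headline figure. No patients are added, and neither the design nor the analysis changes.

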#### Generalizability of the manipulation clinical prediction rule

The CPR developed to predict favorable response to manipulation investigated only one manipulation technique, and predominantly used therapists working within the United States Armed Forces. The accuracy of the CPR for predicting the outcomes with therapists in other work settings, or using other manipulation techniques is not known. However, recently, Cleland et al [21] utilized a different manipulation technique than that used in the development of the rule in a consecutive series of patients who satisfied the CPR. Eleven of the 12 patients (92%) in this case series that satisfied the CPR and were treated with an alternative lumbar manipulation technique demonstrated a successful outcome (> 50% reduction in the OSW) in 2 visits. It is plausible that patients with LBP who satisfy the CPR may obtain a successful outcome with different manipulation techniques directed at the lumbopelvic region. However, the inherent limitation of a case series does not allow us to infer a cause and effect relationship between the manipulation and the patient's outcomes. Although some clinicians have argued for superior efficacy with certain techniques recent evidence questions this belief. Chiradejnant et al [22] examined 140 patients with LBP and found no difference in outcomes between patients who received the mobilization technique selected by the treating therapist or a randomly selected technique. Another debate among clinicians is the need to perform thrust manipulation techniques versus non-thrust mobilization techniques. A recent review by Bronfort et al [23] examined the evidence for both thrust manipulation and non-thrust mobilization and concluded that the evidence favors the use of manipulation, particularly for patients with acute LBP, but more studies are needed comparing the different forms of treatment.

The purpose of the present study is therefore to conduct a multi-center randomized clinical trial to compare the outcomes of three different manual therapy techniques in patients with LBP who fit the spinal manipulation CPR. The three techniques used will be; 1) the thrust manipulation technique used in the development of the CPR, 2) an alternative lumbar thrust manipulation technique, and 3) a non-thrust lumbar mobilization technique. A variety of clinicians in geographically diverse practice settings will be used to permit comparison of outcomes within different practice settings.

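### The aim of comparing outcomes in different practice settings rests only on within-location power, which cannot show whether effects differ between settings; add an exploratory treatment-by-site term with site estimates

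*Protocol article*

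**What the plan says.** In the Background (*Generalizability of the manipulation clinical prediction rule*), the article notes that the rule's accuracy in other work settings is unknown. It closes the purpose statement by saying that varied clinicians and settings "will be used to permit comparison of outcomes within different practice settings".

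The statistical counterpart is in *Data analysis*. "We will recruit 60 patients per clinical site, for a total enrollment of 240 patients across the four geographical locations". Two power statements follow: 93% for 5 points in the whole sample, and, per site, "A sample size of 60 within each geographical location will provide 83% power to detect a difference of 9 points on the OSW", both with a standard deviation of 10. The section then summarises: "This sample size will provide sufficient power to detect a minimum clinically important difference in the entire sample, and a moderate difference within a geographical" site.

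The primary ANOVA is specified as follows: "The independent variable will be treatment with three levels (lumbo-pelvic manipulation, alternative lumbar manipulation, lumbar mobilization"). The analyses at one week, at six months and of pain follow the same procedure. Site appears in none of them, although *Randomization* provides a separate list for each site.

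**The concern.** The quantity that was powered does not answer the question about settings. A test inside one location asks whether the three techniques differ there. Whether they differ by another amount elsewhere is a question about the treatment-by-site contrast, and the models as described cannot address it.

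The natural use of a within-location power statement is to test each location and compare the verdicts. With about 20 patients per arm, sampling error alone will often make some sites significant and others not. A reader could take that pattern as evidence that effectiveness depends on the setting, which would be a false conclusion on the generalizability question that motivates the multi-centre design.

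The word moderate adds to the problem. Nine points is 9/10 = 0.9 SD, and 9/5 = 1.8 times the 5 points that the article treats as its minimum clinically important difference.

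**Working it through.** **Inputs** (*Data analysis*): 240 patients, 60 at each of four sites; effects of 5 and 9 points; SD 10; alpha 0.05 ("alpha level of 0.05 will be used for all analyses"). Assumed: 1:1:1 allocation (the ratio is not stated), so 80 per arm overall and 20 per arm per site; SD 10 in every cell; no dropout, as in the article's power statements.

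**1. Reproducing the stated power.** The omnibus F test has noncentrality λ = n·Σ(μᵢ − μ̄)²/σ². If one arm differs from the other two by d, the sum is 2d²/3. If the means are evenly spaced (0, d/2, d), it is d²/2.

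- Site, d = 9, one arm differs: λ = 20 × 54/100 = 10.8 on 2 and 57 df; power 82.5% (stated 83%).
- Overall, d = 5, one arm differs: λ = 80 × 16.67/100 = 13.3 on 2 and 237 df; power 91.2% (stated 93%).
- Evenly spaced means: site λ = 20 × 40.5/100 = 8.1, power 69.9%; overall λ = 80 × 12.5/100 = 10, power 81.0%.

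Of the variants tried (these two patterns, and one- and two-sided pairwise tests), only the one-arm-differs ANOVA comes within two points of both stated figures.

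**2. Four separate site tests when the true effect is the same everywhere.** With power p per site and independent sites, P(split verdict) = 1 − p⁴ − (1 − p)⁴.

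| Common effect | Pattern | p per site | p⁴ (all four) | (1 − p)⁴ (none) | Split |
|---|---|---|---|---|---|
| 0 | none | 0.050 | 0.000 | 0.8145 | 0.1855 |
| 5 | one arm differs | 0.3371 | 0.0129 | 0.1932 | 0.794 |
| 5 | evenly spaced | 0.2612 | 0.0047 | 0.2979 | 0.697 |
| 9 | one arm differs | 0.8251 | 0.4634 | 0.0009 | 0.536 |
| 9 | evenly spaced | 0.6988 | 0.2385 | 0.0082 | 0.753 |

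Simulation (20,000 trials per row) gave split rates of 18.7%, 79.8%, 69.5%, 53.5% and 75.3%, in the same order.

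The split rate exceeds one half only when p lies between about 0.16 and 0.84. That corresponds to a common effect of about 3.2 to 9.2 points (one arm differs) or 3.7 to 10.6 points (evenly spaced). At 12 points it is down to 9% and 28% respectively.

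**3. The treatment-by-site test.** It has (3 − 1)(4 − 1) = 6 numerator df and 240 − 12 = 228 error df. When site effects are identical it was significant in 4.8–5.2% of simulated trials. For its power, let one arm differ by d at some sites and by 0 at the others; λ = 20·ΣI²/100, where I are the interaction effects.

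- One site against three: ΣI² = d² × (3/4) × (2/3) = d²/2. For d = 5, λ = 2.5 and power is 17%; for d = 9, λ = 8.1 and power is 52%.
- Two sites against two: ΣI² = d² × 1 × (2/3) = 2d²/3. For d = 5, λ = 3.3 and power is 22%; for d = 9, λ = 10.8 and power is 67%.

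**4. Precision within a site.** A difference between two arms has standard error 10 × √(1/20 + 1/20) = 3.16, so a 95% interval is roughly ±1.96 × 3.16 = ±6.2 points, wider than the 5-point difference of interest.

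**The case against.** The strongest reply is that the article schedules no site-level test. It lists its ANOVAs, and the only mention of locations is in the sample-size rationale. A reader might infer that four separate site ANOVAs are planned and that their verdicts will be compared; the text does not say so, and the split rates apply only if the provision is used in that way. This part of the objection stands.

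Secondly, the article condenses a fuller protocol that is not shown, and a site term may be specified there. So the missing term alone would not be a finding. What remains is visible on the page: the article states an aim about settings and supports it with a quantity that does not serve it.

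Thirdly, comparing outcomes *within* settings can be read as replicating the technique comparison in each setting, not as testing heterogeneity between them. That reading is fair. Even so, at 26–34% power for 5 points, within-site significance is a poor measure of replication, and estimates with intervals serve that purpose better.

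Fourthly, the interaction test is itself weak, and a non-significant result could be misread as consistency across sites. That is correct, and it limits what the fix can deliver.

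**Conclusion.** The point holds as a mismatch between a stated aim and its only stated statistical support. At both effect sizes that the article uses, separate site tests would give split verdicts in more than half of trials with identical true effects: 70–79% at 5 points and 54–75% at 9 points.

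Two stronger readings are not supported. One is that site verdicts would conflict in most trials whatever the truth. The rate is about 19% if the techniques are equivalent, which the Background treats as plausible, and it falls below half for large effects. The other is that the 83% is a miscalculation. It reproduces (82.5%) when one arm differs from the other two; what is missing is that condition, since evenly spaced means give about 70%.

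The pooled primary test is not invalidated. The figures rest on equal allocation within sites, SD 10 throughout and no dropout. The change is worth making because it is cheap and protects the generalizability conclusion.

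**What to change.** Change the wording of *Data analysis* in four ways:

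- Add site, already the randomisation stratum, as a factor in the pooled ANOVA. This takes 3 df (error df 240 − 1 − 2 − 3 = 234, against 237 without it).
- In a second fit, add the treatment-by-site term (6 df), labelled exploratory. Report the treatment differences at each site with 95% confidence intervals.
- State that no conclusion about settings will be drawn from within-site p-values, or from a non-significant interaction, and give the interaction's approximate power (17–22% for a 5-point and 52–67% for a 9-point between-site difference).
- Describe the 9-point within-location difference as large (0.9 SD). State that the 83% assumes one arm differing from the other two, and that it is about 70% if the means are evenly spaced.

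No extra patients, visits or data are needed. The cost is accepting openly that four sites of 60 can describe differences between settings but can test them only weakly.

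### Covariates are to be chosen by significance tests on baseline differences, so chance imbalance and an undefined judgement can alter the primary model, and prognostic variables such as baseline OSW usually go unadjusted

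*Protocol article*

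**What the plan says.** All of the relevant text is in the Data analysis section of the protocol article.

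- Purpose of the baseline comparison: "Baseline demographic data will be compared across treatment groups to assess the adequacy of the randomization".
- Rule for adjustment, which the plan opens with the qualifier *if appropriate* and does not define further: "statistical adjustments will be made for baseline characteristics that are significantly different between groups".
- Threshold: an "alpha level of 0.05 will be used for all analyses", which covers the baseline tests as well.
- Primary model: "The primary aim will be tested with analysis of variance (ANOVA) using the change in OSW score from baseline to 4-weeks". Its only term is treatment: "The independent variable will be treatment with three levels (lumbo-pelvic manipulation, alternative lumbar manipulation, lumbar mobilization"). The Abstract (Methods/Design) states the same model.

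No covariate is named in advance. Baseline OSW, pain rating and FABQ are all collected at baseline (Examination procedures). Symptom duration and FABQ-W are also eligibility items (Study sample). Randomisation lists are generated separately for each site (Randomization).

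**The concern.** Three things look wrong.

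1. **The test answers the wrong question.** If the lists and envelopes work as described, every baseline difference is due to chance, and a p-value below 0.05 turns up at the nominal rate. It is therefore a weak check on randomisation.
2. **The trigger selects on the wrong property.** A covariate is worth having because it predicts the outcome. This rule asks only whether it happened to differ between arms, so a strong predictor and an irrelevant variable have the same chance of entering.
3. **The model is settled late.** Whether anything is added to the treatment-only ANOVA, and what, depends on the allocated data and on a judgement for which the article gives no criterion. The text does not say whether an adjusted analysis would replace the primary one or stand beside it.

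At stake are the precision of the primary comparison and the certainty, before data are seen, of which analysis is primary.

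**Working it through.** **Inputs.** From Data analysis: N = 240, difference 5 OSW points, SD 10, alpha 0.05. Assumed: equal arms (80 each); SD 10 at baseline and at 4 weeks; baseline to 4-week correlation r = 0.3, 0.5 or 0.7; number of baseline variables tested m = 5, 10 or 15.

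**Step 1: the plan's own power figure.** The plan says "A sample size of 240 patients will provide 93% power to detect a minimal difference of 5 points on the OSW". For a three-arm F test with one arm differing by d, the noncentrality is λ = n·(2/3)·d²/SD² = 80 × (2/3) × 25/100 = 13.33, which gives 91.2%. A one-sided two-arm comparison gives 93.5%. The stated 93% is thus reproduced to within 2 points.

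**Step 2: how often the trigger fires.** Under valid randomisation each variable is significant with probability 0.05. For m independent tests, P(at least one) = 1 − 0.95^m:

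- m = 5: 22.6%
- m = 10: 40.1%
- m = 15: 53.7%

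Any given variable is left out with probability 95%, however well it predicts outcome. Simulated entry rates for one covariate were about 5% at every correlation tried.

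**Step 3: variance forgone for baseline OSW.** With equal SD σ at both times:

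- change score: 2σ²(1 − r)
- ANCOVA: σ²(1 − r²)
- ratio, ANCOVA to change score: (1 + r)/2

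| r | Change-score variance | ANCOVA variance | Reduction |
|---|---|---|---|
| 0.3 | 140 | 91 | 35% |
| 0.5 | 100 | 75 | 25% |
| 0.7 | 60 | 51 | 15% |

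With unequal SDs s₀ (baseline) and s₁ (4 weeks), the change-score variance exceeds the ANCOVA variance by (s₀ − r·s₁)², which is never negative. The direction therefore does not depend on the equal-SD assumption; the size does.

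**Step 4: power, one arm differing by 5 points.** λ = 80 × (2/3) × 25/variance = 1333.3/variance. The column for the rule is simulated.

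| r | λ change | Power, no adjustment | Power, protocol's rule | λ ANCOVA | Power, ANCOVA |
|---|---|---|---|---|---|
| 0.3 | 9.52 | 79.0% | about 80% | 14.65 | 93.6% |
| 0.5 | 13.33 | 91.2% | about 92% | 17.78 | 97.1% |
| 0.7 | 22.22 | 99.1% | above 99% | 26.14 | 99.7% |

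The rule does barely better than never adjusting.

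If the plan's SD of 10 is instead read as the SD of the change, power without adjustment is 91.2% at every r. ANCOVA has λ = 13.33/[(1 + r)/2] = 20.51, 17.78 or 15.69, so power of 98.6%, 97.1% or 95.1%.

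**Step 5: type I error of the mechanical rule.** Simulation under the null (50,000 trials per r, baseline OSW the only candidate) gave 4.1%, 4.4% and 4.5% at r = 0.3, 0.5 and 0.7. The reason shows at r = 0.5. The unadjusted test rejects in 4.31% of the 94.9% of trials without significant imbalance and in 17.06% of the other 5.1%: 0.949 × 4.31% + 0.051 × 17.06% = 5.0%. The rule swaps the second part for ANCOVA, which rejects 5.25% there: 0.949 × 4.31% + 0.051 × 5.25% = 4.4%.

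**The case against.** The strongest reply is that the primary analysis is in fact stated, in both the Abstract and Data analysis, and that the adjustment sentence is general, qualified and does not name it. This stands in part. A reader might infer that the primary model is not prespecified at all or is decided by chance, and the documents do not support that. What remains is that the sentence precedes all the inferential analyses, exempts none, and leaves open whether an adjusted result can displace the default.

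A reader might also infer inflated false positives. Step 5 shows the opposite for the mechanical rule: it is slightly conservative. The discretion in the qualifier is a separate matter that the simulation does not measure.

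The outcome is already a change from baseline OSW, so baseline is not ignored. That is true, but subtracting baseline does not adjust for its association with change. In the 5% of null trials with significant OSW imbalance, the unadjusted change-score test rejected between 13% and 24% of the time across the three correlations.

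Baseline tests are not entirely void, since a gross imbalance could point to a failure of the envelope process. They are a weak tool for that, and this use gives no reason to let them choose covariates.

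Finally, the eligibility floor of 25% on OSW restricts the baseline range, and baseline measures are likely to be correlated. Both limit how literally the figures in Steps 2 to 4 can be taken.

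**Conclusion.** The point holds as a defect in a rule that the protocol states, not as a missing detail. The rule chooses covariates by baseline p-value, leaves a predictor such as baseline OSW unadjusted about 95% of the time, and allows the fixed default model to be altered after allocated data are seen.

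The size depends on a correlation that the protocol does not give. With equal SDs of 10 and one arm differing, the power forgone is roughly 13 to 14 percentage points at r = 0.3, 5 at r = 0.5 and under 1 at r = 0.7. No single figure, such as the 25% variance reduction at r = 0.5, should be quoted without this range.

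Nor should it be read as showing that the trial misses its stated power. At r = 0.5, where the change score has the planned SD of 10, power under the rule is about 92%, close to the stated 93%. The loss there is precision that could have been had free. The change should be made, but the primary test is not invalid without it.

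**What to change.** Delete the baseline significance tests and the adjustment trigger. Present baseline characteristics by arm descriptively. In both places where the primary analysis is stated (Abstract, Methods/Design; Data analysis), replace the ANOVA by an ANCOVA of 4-week OSW with treatment, baseline OSW and site as terms, fitted whatever the observed imbalance. Using the change as the dependent variable gives the same treatment estimates once baseline OSW is a covariate. Site belongs in the model because the randomisation lists are separate by site. Label any further adjustment as a sensitivity analysis that does not replace the primary result.

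The cost is a few sentences in two sections. No new data or patients are needed, since baseline OSW and site are already recorded. The added terms use 1 + 3 = 4 of the 237 residual degrees of freedom, which has a negligible effect on power.
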